### Outcomes

#### Primary Outcome Indicator

The primary outcome measure will be the change in visual analog scale score relative to baseline at 4 weeks.

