**Methods:**

This will be a single-center randomized controlled trial. A total of 116 eligible patients with brachial plexus injury will be randomly divided into an experimental group (naprapathy plus physical therapy group) or a control group (physical therapy group). The participants will be followed up for 4 weeks of treatment. Observation outcomes will include the visual analog scale score, upper limb index, electromyography findings, and adverse reactions, among others. The measuring points for outcomes will be the baseline and the completion of treatment. In addition, a quality control group independent from the research team will be set up to control the quality of the trial. Finally, the data will be analyzed using SPSS software (version 21.0; IBM Corp).

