#### Secondary Outcome Indicators

The secondary outcomes will include the upper limb motor function score according to the Brunnstrom functional assessment and electromyography findings.

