### Sample Size

Our previous study indicated that 58.5% of patients with BPI showed improvements in upper extremity function and muscle strength [23]. In this clinical trial, the rate of upper extremity function recovery is expected to be 75% in the naprapathy group and 55% in the physical therapy group. With α=.05 and β=.01, a total of 52 participants will be needed, as calculated using SPSS software (version 21.0; IBM Corp). According to the previous study, a 10% withdrawal rate will also be considered; therefore, each group will include at least 58 participants.

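### The sample size rests on a binary upper-extremity recovery rate, while the primary outcome is change in VAS pain, so the stated α and β do not describe the primary comparison

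*Protocol article*

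**What the plan says.** Under Primary Outcome Indicator, the protocol article states: "The primary outcome measure will be the change in visual analog scale score relative to baseline at 4 weeks". This is a continuous pain measure, and it is the only outcome named primary.

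Under Secondary Outcome Indicators it says: "The secondary outcomes will include the upper limb motor function score according to the Brunnstrom functional assessment and electromyography findings". Table 1 adds participant self-evaluation and adverse events. No recovery or responder rate appears in either place, and no threshold for recovery is given.

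The Sample Size section starts from an earlier study in which "58.5% of patients with BPI showed improvements in upper extremity function and muscle strength". It then assumes that "the rate of upper extremity function recovery is expected to be 75% in the naprapathy group and 55% in the physical therapy group". It continues: "With α=.05 and β=.01, a total of 52 participants will be needed, as calculated using SPSS software", and finally: "a 10% withdrawal rate will also be considered; therefore, each group will include at least 58 participants". Neither this section nor any other gives an expected VAS difference or a standard deviation of VAS change.

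**The concern.** A sample size calculation tells the reader what the trial can detect on the outcome that decides it. Here the only calculation concerns a different outcome, of a different type (binary, not continuous) and in a different domain (function, not pain). A reader who sees β=.01 may take the trial to have 99% power for its primary comparison, and nothing in the document supports that.

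The stake is mainly how a null VAS result would be read. The Statistical Analysis section treats a P value above .05 as showing no difference between the groups. Without a stated detectable VAS difference, nobody can judge whether a non-significant result excludes an effect that matters. The undefined recovery rate is a smaller problem. If it were reported later, its cut-off would have to be chosen in an open-label trial that had already enrolled 100 of its 116 participants by January 2023.

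**Working it through.** **1. Inputs from the document.** Sample Size: recovery 75% and 55%; α=.05 (sidedness not stated); β=.01; 52 participants; 10% withdrawal; 58 per group. Randomization: 1:1, 116 in total. VAS difference and SD: none given.

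**2. What 52 means.** The text calls 52 a total. The withdrawal step is 52 / (1 − 0.10) = 57.8, rounded up to 58. The document says 58 per group, and 2 × 58 = 116, so 52 has to be per group. As a total it would lead to 58 participants overall. I use 52 evaluable per group below, which departs from the literal wording.

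**3. The plan's own figure.** For two proportions, with mean p̄ = (0.75 + 0.55)/2 = 0.65:

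n per group = [z(α/2)·√(2p̄(1−p̄)) + z(power)·√(p₁(1−p₁) + p₂(1−p₂))]² / (p₁−p₂)²

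At two-sided .05 and 99% power:

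- [1.960·√0.455 + 2.326·√0.435]² / 0.04 = (1.322 + 1.534)² / 0.04 ≈ 204 per group
- one-sided: 175 per group
- 90% power: 118 two-sided, 96 one-sided
- 80% power: 89 two-sided, 70 one-sided

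None of these gives 52. With 52 per group, power for 75% against 55% is Φ[(0.2·√52 − 1.322)/0.660] = Φ(0.18) ≈ 57% two-sided. This is a separate error. It matters here only because it means the stated power cannot be borrowed from the functional endpoint either.

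**4. What the fixed size can detect on VAS.** For a two-sample t test, two-sided .05, the normal approximation is d = (z(α/2) + z(power))·√(2/n). At n = 52 and 80% power, d = (1.960 + 0.842)·√(2/52) = 0.549. The exact noncentral-t values are slightly larger:

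| Evaluable per group | d at 80% | d at 90% | d at 99% |
|---|---|---|---|
| 52 | 0.555 | 0.642 | 0.849 |
| 58 | 0.525 | 0.607 | 0.803 |

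In the other direction, power with 52 per group is about 52% for d = 0.4, 71% for d = 0.5 and 86% for d = 0.6.

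**5. In VAS points.** Both the 0–10 scale and the SD of VAS change are assumptions; the document gives neither. Detectable difference = d × SD, with 52 per group:

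| Assumed SD | 80% power | 90% power |
|---|---|---|
| 2.0 | 1.1 | 1.3 |
| 2.5 | 1.4 | 1.6 |
| 3.0 | 1.7 | 1.9 |

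**The case against.** The strongest reply is that nothing here harms the VAS analysis itself. The number of participants is fixed and nearly reached. The mismatch neither biases the VAS estimate nor inflates its type I error, and a detectable d of about 0.555 at 80% power is a moderate effect. That stands: the absence of a stated power is not evidence of low power.

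Three stronger readings are tempting, and the document does not support them.

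- **Two competing main endpoints.** A reader might infer this from the Sample Size section. But only VAS change is called primary, function is placed among the secondary outcomes, and the Sample Size section never calls the recovery rate primary.
- **The functional hypothesis is never tested.** Upper-limb function is measured at baseline and after treatment and is a secondary outcome. What is missing is a definition of recovery, not the functional question.
- **Proportions cannot be analysed.** The Statistical Analysis section plans a generalized linear model, a class that includes models for binary outcomes. The details for a secondary outcome may also sit in a fuller document that is not shown.

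Nor can the abstract's term, an upper limb index, be pinned to the Brunnstrom score. It is loose wording with no bearing on power.

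The appeal to condensation does not rescue the main point. The article does give its basis for the sample size, and that basis belongs to another endpoint.

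**Conclusion.** The point holds as a mismatch between the endpoint that sets the number of participants and the endpoint that decides the trial. The stated α and β do not describe the VAS comparison. No assumption about VAS is given from which its power could be worked out, and the recovery rate used instead is not a listed or defined outcome.

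It does not follow that the trial is too small for VAS. With 52 evaluable per group it has 80% power if the true standardized difference is about 0.555 and 90% if it is about 0.64. Whether that is enough depends on an effect and an SD that the document does not state. These figures rest on reading 52 as per group, a two-sided .05 t test and full follow-up of those 52. The values in points also rest on the assumed 0–10 scale and SD of 2 to 3.

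**What to change.** Keep VAS change at 4 weeks as the single primary outcome and keep 116 participants. In the Sample Size section:

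- State that the number was not derived from VAS, and remove any implication that β=.01 applies to the primary outcome.
- Report the VAS difference detectable at the fixed size with 80% and 90% power. Declare the scale, the assumed SD and its source, the sidedness, and that 52 is per group.

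Keep the Brunnstrom score as the secondary functional outcome. Do not turn 75% and 55% into a new Brunnstrom responder endpoint: the document does not tie those rates to that scale, and most participants were already enrolled without blinding. If a recovery rate is reported, label it exploratory unless its threshold is fixed before anyone sees outcome data by group.

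The cost is a wording amendment and a registry update before the data are analysed, with no added patients or visits. The downside is saying openly that the trial was not sized on its primary outcome.

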#### Secondary Outcome Indicators

The secondary outcomes will include the upper limb motor function score according to the Brunnstrom functional assessment and electromyography findings.

### Time Points of Outcome Measurement

Outcomes will be evaluated at 2 time points: baseline and at the completion of treatment. An overview of the outcomes measured at the different time points is shown in Table 1.

**Table 1 table1:** Case data collection timetable.

Time point	Baseline	Posttreatment
Written informed consent	✓	
Concomitant treatment	✓	
Disease history	✓	
History of medication	✓	
Brunnstrom functional assessment	✓	✓
VAS^a^	✓	✓
EMG^b^ examination	✓	✓
Participant self-evaluation		✓
Adverse events		✓
Safety analysis		✓

^a^VAS: visual analog scale.

^b^EMG: electromyography.

### Assessment of Safety and Adverse Events

According to clinical experience and the literature, naprapathy may cause several kinds of adverse events, such as subcutaneous hematoma, edema, skin bruising, local pain, and fainting. Among these adverse events, subcutaneous hematoma and edema are the most common. Naprapathy-related safety and adverse events will be carefully recorded using case report forms. Adverse events should be reported to the ethics committee of Yueyang Hospital affiliated with the Shanghai University of Traditional Chinese Medicine. The Ethics Committee has the right to stop the intervention of the participant.

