### Patient and Public Involvement

Patients and the public are involved in the design of the study. They reviewed the study proposal and attended the design meetings. Patients and the public will be included in all research communications.

The inclusion criteria are as follows: (1) aged 18 to 70 years; (2) BPI diagnosed by history, physical examination, electromyography, or surgical exploration more than 2 weeks after nerve surgery; (3) agreement to provide written informed consent.

The exclusion criteria are as follows: (1) concurrent damage to major organs, such as the heart, kidneys, liver, and so forth; (2) severe cardiovascular or cerebrovascular disease, liver or kidney dysfunction, metabolic disease, or mental illness; (3) chronic illness, physical discomfort, frailty, severe neurosis, or pregnancy; (4) primary brachial plexus pain or brachial plexus neuritis; (5) brachial plexus pain due to cervical spondylosis, tennis elbow, carpal tunnel syndrome, frozen shoulder, biceps tenosynovitis, thoracic outlet syndrome, or other secondary causes.

The participants will be withdrawn if they have the following: (1) missing or incomplete patient treatment records, which would affect the final data analysis; (2) treatment with other methods at the same time; (3) any severe adverse reactions or other emergent symptoms during the treatment (such as aggravation of disease or severe depression and the need for special treatment).

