### Data Collection and Management

All our measures will be free of charge to ensure complete participation in the follow-up evaluation. Case report forms will be completed in paper form and stored by the Shanghai University of Traditional Chinese Medicine. Data will be collected according to Table 1 by investigators, and personal information about the enrolled participants will be kept in Yueyang Hospital in order to protect confidentiality in the whole trial. The ethics committee of Yueyang Hospital affiliated with the Shanghai University of Traditional Chinese Medicine will audit the trial every 12 months and will establish a data monitoring committee, which is independent from the funder and has no competing interests. The data will be stored in the clinical trial public management platform and ready for public inquiry after the trial. A quality control group independent from the research team will be set up to control the quality of this study.

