### Statistical Analysis

All data will be analyzed by researchers using SPSS (version 21.0) software. Data will be expressed as the mean (SD) or median (IQR). First, the data will be tested for normality and homogeneity of variance; if the data meet the requirements for a normal distribution, the homogeneity of variance will be analyzed by the *F* test. In the case of heterogeneity, the corrected *t* test will be used. If the requirements for normality and homogeneity of variance are not satisfied, the rank-sum test will be used. If the sphericity test yields a *P* value less than .05, indicating that the assumption of sphericity is violated, we will perform multivariate analysis. A statistically significant result (*P*<.05) for the time factor will indicate that the measurements show a trend of changing over time. A statistically significant (*P*<.05) interaction between time and group will indicate that in addition to the effect of time, there are differences between the groups. If a *P* value is less than .05, the difference will be considered statistically significant, indicating a difference in the results between the two groups. If a *P* value is greater than .05, then the difference will not be considered statistically significant, indicating no difference in the results between the two groups. Cohen *d* (sample size) will also be used to compare differences between groups, and the generalized linear model will be applied to explore differences in outcomes between groups.

For safety analysis, adverse event data are generally expressed as the number of events and the percentage of cases involved in the adverse event.

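### The case report form rule for adverse events is worded as naprapathy-related, which conflicts with the unrestricted wording elsewhere, and Table 1 places adverse events at post-treatment only

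*Protocol article*

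**What the plan says.** Under Assessment of Safety and Adverse Events, the article first gives the events expected from the test treatment: "naprapathy may cause several kinds of adverse events, such as subcutaneous hematoma, edema, skin bruising, local pain, and fainting". No such list is given for electrotherapy or continuous passive motion. The recording rule follows: "Naprapathy-related safety and adverse events will be carefully recorded using case report forms". The reporting rule comes directly after it and has no such qualifier: "Adverse events should be reported to the ethics committee of Yueyang Hospital".

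Other sections are also unrestricted. The abstract's Methods paragraph says: "Observation outcomes will include the visual analog scale score, upper limb index, electromyography findings, and adverse reactions, among others". The withdrawal criteria, which stand under Patient and Public Involvement, apply to participants generally and include "any severe adverse reactions or other emergent symptoms during the treatment". Data Collection and Management says: "Data will be collected according to Table 1 by investigators". Table 1 has a plain adverse events row with no split by arm.

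On timing, Time Points of Outcome Measurement says: "Outcomes will be evaluated at 2 time points: baseline and at the completion of treatment". Table 1 ticks adverse events in the post-treatment column only.

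On analysis, Statistical Analysis says: "adverse event data are generally expressed as the number of events and the percentage of cases involved in the adverse event". It states no between-arm comparison of safety.

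**The concern.** The trial asks what naprapathy adds to physical therapy, and adverse reactions are among its named outcomes. The added harm can be seen only if events are found and recorded in the same way in both arms. A rule that turns on relatedness to naprapathy does not do this. Group B cannot have a naprapathy-related event, and in an open-label trial the judgement of relatedness in group A is made with the allocation known.

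Some of the expected events, such as edema and local pain, could also come from the injury or from the physical therapy that both arms receive. The Introduction itself names pain and swelling as problems that physical therapy is meant to treat. Without the same record in group B, background events in group A cannot be told apart from effects of naprapathy.

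Timing is a separate issue. Bruising, local pain and fainting can pass quickly, and a single entry after 4 weeks may miss them.

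**Working it through.** The document gives no adverse event rate or other safety figure, so there is no stated number to reproduce. The check compares the wording of the sections.

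1. **Scope of the form.** The recording sentence is the only one that says which events go on the case report form, and its wording is naprapathy-related. No parallel sentence covers events from physical therapy or from any cause.
2. **Effect on group B under the literal reading.** The Interventions section gives group B physical therapy alone. Its count of naprapathy-related events is then 0 by definition, whatever happens to its participants.
3. **Effect on group A under the literal reading.** An event is recorded only if it is first judged related. Study Design describes the trial as open-label, so that judgement is not masked. The article does not say who makes it or when.
4. **The wider wording.** The ethics reporting sentence, the Table 1 row, the instruction to collect data by Table 1, the abstract's outcome list and the withdrawal criterion all refer to adverse events or reactions without limiting them to one arm. Staff could follow either the narrow or the wide wording.
5. **Timing.** Treatment runs 5 sessions a week for 4 weeks, 5 × 4 = 20 sessions, and Table 1 has one adverse event entry, at the end. This applies to both arms alike, so the risk is under-recall and not exclusion of one arm. A participant withdrawn for a severe reaction may not reach that entry.
6. **Differences in noticing events.** The sentence on suspending treatment after an adverse event stands in the Naprapathy section, and the Physical Therapy section has no counterpart. Group A also has an extra 20-minute session with a practitioner on each treatment day.

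**Illustration, on assumed inputs.** Suppose 10% of each arm has such an event from background causes and naprapathy adds nothing. With 58 per arm, 0.10 × 58 = 5.8, or about 6 events per arm.

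- All events recorded in both arms: 6/58 v 6/58.
- Literal rule, every group A event judged related: 6/58 v 0/58. One-sided Fisher P = C(58,6)/C(116,6) = (58·57·56·55·54·53)/(116·115·114·113·112·111) = .0136; two-sided 2 × .0136 = .027.
- Literal rule, no group A event judged related: 0/58 v 0/58.

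The same underlying events give three different tables. The 10% rate and the attribution patterns are assumptions, and the protocol plans no such test. The example shows only that the recorded contrast would depend on how events are attributed.

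**The case against.** A reader might infer that the control arm cannot contribute adverse events at all, and that the planned safety percentages therefore cannot be compared between arms. The document does not support that. It nowhere says that only naprapathy-related events are recorded, and in the recording sentence the qualifier may attach to the word safety alone. Table 1 gives group B the same adverse event row as group A. Ethics reporting and the withdrawal criterion cover every participant. The Statistical Analysis section plans counts and percentages and states no comparison between arms, so no stated comparison is invalidated. These objections stand, and they limit the point to a conflict of wording and what follows if the narrow wording is applied.

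The post-treatment tick may mark when a cumulative record is completed; the safety analysis row, plainly an end-of-treatment step, is ticked in the same column. The withdrawal criterion and the suspension sentence also show that events are expected to be noticed during treatment. This stands too, and the timing concern is conditional on it.

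Finally, a journal article may leave event logs and attribution fields to the full protocol or to the form itself. That answers any complaint that such detail is missing. It does not answer this point, because the article does state a recording rule and the rule conflicts with its own other sections.

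**Conclusion.** The concern holds in a limited form. The one stated rule for recording adverse events on the case report form is worded as naprapathy-related and is inconsistent with the unrestricted wording in the same section and in four other places. If staff follow it literally, group B events need not be recorded, relatedness in group A is judged with allocation known before anything is recorded, and percentages set side by side by arm would not be comparable. If staff follow the wider wording, the arms are treated alike and the defect is one of drafting.

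The size cannot be estimated from the document. It depends on the background event rate, which is not given, and on how the sentence is applied in practice. The 6 v 0 example shows what could happen under assumed inputs and does not predict the result. The risk from the single post-treatment entry is under-recall in both arms, and only if that entry is not a running record. The correction is worth making because it removes a possible source of bias at small cost.

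**What to change.** - **Recording sentence.** In Assessment of Safety and Adverse Events, state that all adverse events, whatever their cause, are recorded identically in both arms throughout the 4 weeks, with relatedness to treatment as a separate field that does not decide whether the event is recorded.
- **Table 1.** Change the timing of the adverse events row from post-treatment to throughout treatment.
- **Reporting.** Give the number of events and the percentage of participants affected by arm, including participants who stop early.
- **Coverage.** By January 2023, 100 of 116 participants had been enrolled, leaving 116 − 100 = 16. The report should state which participants were covered by the revised recording. If the forms in use already captured all events in both arms, the report can say so and only the wording needs correcting.

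The cost is a minor form amendment and a little staff time at sessions that already take place from Monday to Friday in both arms. The limit is that a late change cannot repair incomplete records for participants already treated.
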